### Phase II: Feasibility Testing of mDASHNa-CC App

Following usability testing, a pilot randomized controlled trial [61] feasibility study will be conducted with Chinese Canadian seniors to determine implementation (primary outcomes, including accrual and attrition rates, technical issues, acceptability of the app, and adherence to the intervention,) and preliminary effectiveness (secondary outcomes, including systolic and diastolic blood pressure, weight, waist circumference, health-related quality of life, and health service utilization). This study is designed as a pilot two-group (1:1) randomized controlled trial with a sample size of 60 participants (block of 20) in a Chinese Canadian community in the Greater Toronto Area.

The sampling procedures and setting will be the same as the Phase I study. A convenience sample of 60 Chinese Canadian seniors will participate in this study. Self-identified Chinese Canadians were recruited if they met the following inclusion criteria: (1) at least 65 years of age; (2) had a systolic blood pressure between 140 to 159 mmHg or a diastolic blood pressure between 90 to 99 mmHg; (3) were able to understand and speak Mandarin and read and write Chinese; and (4) had access to a smartphone. Individuals were excluded if they: (1) used antihypertensive medications, insulin, or oral hypoglycemic agents; (2) had a cardiovascular event during the previous three months; (3) had a history of congestive heart failure; (4) had a cancer diagnosis or had undergone cancer treatment during the past two years; or (5) had special dietary requirements.

As a pilot study is not powered to be a hypothesis-testing trial, formal sample size calculations are not recommended [62]. Instead, the sample size suggested was based on recommendations for feasibility trials [63]. In this pilot study, 60 eligible participants will be recruited. Following university ethics approval, participants will be recruited by blood pressure screening events in diverse community settings. The recruitment process of Phase II is the same as that of Phase I. Study procedures will commence after eligibility is assessed, informed consent is obtained, and demographic and baseline outcome data are collected by a trained research assistant.

Using an online randomization tool provided by Interrand Company, Ottawa, Canada, participants will be randomized into either an intervention group or a control group. Participants randomized to the intervention group will receive the mDASHNa-CC app intervention for eight weeks plus usual care; participants randomized to the control group will receive usual care. Coinvestigators, collaborators, and outcome assessors will be blinded to the group assignment. Because this study is an app educational intervention, it will be impossible to blind participants to the group assignment. The group assignment will be concealed until all outcome data are collected [64]. After all outcome data are collected eight weeks post-randomization, participants in the control group will also be offered use of the app.

The control group will be usual care. Usual care consists of three parts: (1) receiving a general hypertension health education booklet from the Heart and Stroke Foundation of Ontario; (2) being encouraged to see their family physicians or primary health care providers regarding their blood pressure status (those who do not have a primary health care provider will be referred to a walk-in clinic or a community health center); and (3) having access to family physicians, telehealth, emergency care, hospitals, and other health care facilities in the Greater Toronto Area as required.

In addition to usual care, those participants randomized to the intervention group will be offered use of the app. A trained research assistant will teach them how to use it, they will load the app on their smartphones, and then they will be requested to review educational material, conduct dietary self-assessments, and monitor blood pressure for eight weeks. Telephone assistance from a trained research assistant will be available to seniors in case of technical problems or if any questions arise about the app. The research team will conduct a daily review of a summary of each senior’s report so that participant safety issues can be identified and resolved. By the end of the eight weeks postrandomization, seniors will be prompted by phone using an audible alert to complete the app evaluation questionnaire on their smartphone, which will ascertain likes and dislikes with the app.

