Accrual and attrition rates: The mDASHNa-CC recruitment log has been designed to record data related to the number of eligible seniors per recruitment day, reasons for ineligibility, and reasons for nonparticipation. The mDASHNa-CC Activity Log has been designed to record data on attrition, including occurrence/reasons for attrition, technical difficulties, adherence, and outcome measure completion. A trained research assistant will complete the logs daily during the research process.Technical issues: The occurrence and description of technical problems will be recorded on the mDASHNa-CC activity log by a trained research assistant.Acceptability: The acceptability e-scale ascertains perceptions related to how helpful, difficult, and enjoyable electronic-based programs are to use, how understandable questions are, and how acceptable the time invested in reporting was [65]. This scale demonstrated validity and reliability in various prior studies [65]. For the present study, the wording of the scale will be slightly modified, and a free-text question, where seniors are encouraged to enter any other information that they feel would be important to discuss, will be added. Seniors in the intervention group will fill out this scale by email four weeks and eight weeks postrandomization.Adherence: A built-in number counter will measure participants’ adherence to the requirements of learning dietary educational material, conducting dietary self-assessments, and monitoring blood pressure in the mDASHNa-CC app. The number counter will record the time and frequency of app use. The dietary intake will be measured at baseline and eight weeks postrandomization by a one-to-one dietary interview using the validated Automated Multiple Pass Method [66] by a trained research assistant in the community center. This approach was successfully tested in the DASHNa-CC pilot trial. Adherence to the DASH will be measured by the validated DASH component score of each food group, and the total DASH score [67]. Adherence to the sodium reduction will be measured by a 24-hour urine test [68]. Adherence to TCM food therapy will be measured using a 24-statement questionnaire on a 5-point Likert scale, which was validated in the DASHNa-CC pilot study [69].

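### Phase II publishes a single block size of 20 in an open trial and does not separate enrolling staff from staff who see allocations, so some assignments could be deduced

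*Protocol article*

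**What the plan says.** The Phase II section (Phase II: Feasibility Testing of mDASHNa-CC App) fixes the allocation structure as a "pilot two-group (1:1) randomized controlled trial with a sample size of 60 participants (block of 20" per block. It states no strata and no other block size.

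On mechanism and blinding, the same section says:
- "Using an online randomization tool provided by Interrand Company, Ottawa, Canada, participants will be randomized into either an intervention group or a control group".
- "Coinvestigators, collaborators, and outcome assessors will be blinded to the group assignment". Staff who enrol are not in this list.
- For participants, "it will be impossible to blind participants to the group assignment".
- "The group assignment will be concealed until all outcome data are collected [64".

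On who does what, the role of trained research assistant recurs:
- Before allocation: "Study procedures will commence after eligibility is assessed, informed consent is obtained, and demographic and baseline outcome data are collected by a trained research assistant".
- After allocation, in the intervention arm: "A trained research assistant will teach them how to use it, they will load the app on their smartphones". The same role title gives that arm telephone help.
- In the Phase II Measurement Tools section, the "recruitment log has been designed to record data related to the number of eligible seniors per recruitment day", together with reasons for ineligibility and nonparticipation. A separate activity log covers attrition, technical difficulties and adherence. A trained research assistant fills in both logs each day.

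**The concern.** An outside online tool hides the list. It cannot hide the remainder of a block of known length from someone who has counted the allocations so far. In a 1:1 block of 20, once one arm has reached 10 the rest is settled. Before that, the arm that is behind is the better guess.

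The concealment sentence does not close this gap. It cannot be true of participants or of the assistant who installs and teaches the app. It also describes keeping assignments from others after they are made, which is blinding. Concealment in the sense that matters here means that the person deciding whether to enrol the next senior cannot foresee the next assignment.

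There is some room to act on a guess, because sampling is by convenience at screening events and entry depends on a blood pressure reading within a range. Two of the primary outcomes come from the app arm alone: acceptability is collected only there, and app-use adherence comes from a counter inside the app. If people more at ease with smartphones entered that arm preferentially, these results would look better than they should. The blood pressure comparison, a secondary outcome, would be exposed in the same way.

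**Working it through.** **Inputs.** N = 60, ratio 1:1 and block size 20 come from the Phase II section. The predictability figures assume an observer who knows the block size and every earlier allocation.

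**Structure.** 60/20 = 3 complete blocks of 10 + 10, so 30 per arm. The stated design is arithmetically consistent.

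**Certain assignments.** With m = 10 per arm in a block of 2m = 20, the probability that at least the last k assignments are certain is 2·C(20−k,10)/C(20,10), where C(20,10) = 184,756:
- k = 1: 2·92,378/184,756 = 100%
- k = 2: 2·43,758/184,756 = 47.4%
- k = 3: 2·19,448/184,756 = 21.1%
- k = 4: 2·8,008/184,756 = 8.7%

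The expected number is 2m/(m+1) = 20/11 = 1.82 per block. Over three blocks that is 5.45 of 60, or 9.1%.

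**Correct guesses.** Always guessing the arm that is behind, and tossing a coin at ties, gives m + ½(4^m/C(2m,m) − 1) correct per block. Here 4^10/184,756 = 5.675, so the result is 10 + ½(4.675) = 12.34 of 20. That is 61.7%, or 37.0 of 60.

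**Worst-case bias.** Suppose staff act on every guess and thereby shift the expected outcome of the next person by +d or −d. With correct-guess rate p, the between-arm difference is biased by 2(2p − 1)d. For p = 0.6169 this is 0.47d. The documents give no value for d. If d is assumed to be 1 to 3 mmHg, the bias is 0.5 to 1.4 mmHg. The systolic difference in the earlier classroom pilot was 3.8 mmHg (P=.12).

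**Alternatives.** Fixed blocks are exact; the mixed-block and imbalance-limit rows are simulations of lists of 60.

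| Scheme | Certain, of 60 | Correct guesses (p) | 2(2p − 1) | Final arm difference: mean, 95th percentile |
|---|---|---|---|---|
| Fixed 20 (as stated) | 5.5 | 61.7% | 0.47 | 0, 0 |
| Fixed 8 | 12.0 | 66.6% | 0.66 | not compared |
| Fixed 4 | 20.0 | 70.8% | 0.83 | not compared |
| Random 4/6/8 | not computed | 67.8% | 0.71 | not compared |
| Random 16/20/24/28, sizes withheld | 0 | 60.3% | 0.41 | 1.4, 4 |
| Big-stick limit of 8, withheld | 0 | 52.0% | 0.08 | 4.0, 8 |

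The big-stick rule is a fair coin except when the arms differ by 8. Forced assignments are always guessed right and the rest half the time, so about 60 × (0.52 − 0.50)/0.5 = 2.4 of 60 are forced. They cannot be recognised as certain while the limit is withheld.

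**Cost in precision.** Variance relative to 30/30 is (1/n₁ + 1/n₂)/(2/30). A split of 32/28 gives 1.004. A split of 34/26, the largest that the limit of 8 allows, gives 1.018, a loss of 1.8%.

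**The case against.** The strongest reply is that the article never says that enrolling staff see each allocation. A trained research assistant is an indefinite role title and may cover several people. The Phase II sentence on eligibility, consent and baseline data ties the assistant clearly only to data collection, and the parallel Phase I sentence leaves the eligibility assessor unnamed. This stands: overlap of roles is an inference from the shared title and from one role keeping both logs. Who enrols and who sees assignments is also a detail that a condensed article may leave to the full protocol. The point therefore rests on the stated block size and the stated concealment sentence, with the overlap as a condition.

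A reader might also infer that the closing run of each block is known in advance. That is too strong. Only the last assignment is always certain, and in 52.6% of blocks it is the only one. Nor is 20 a poor choice among block sizes, since smaller blocks are more predictable.

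The safeguards count too. The tool is external, several roles are blinded, controls are offered the app after week eight, and the recruitment log would leave a trace of eligible seniors who were not enrolled. These weaken motive and opportunity. None of them makes the next assignment unpredictable to someone who has kept count.

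Finally, the worst case needs complete knowledge, a guess at every enrolment and success each time, and its mmHg range has no basis in the documents. That is correct, so the size should be read from the predictability figures and not from mmHg.

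**Conclusion.** The point holds as a conditional exposure. The article publishes one block size for a trial that is open to participants and to the staff who teach the app. It does not separate those staff from the ones who enrol, and its concealment statement does not protect the next assignment. If the same people do both, about 5.5 of 60 assignments (9%) are deducible on average, at least 3 of them with certainty (the last of each block), and the best guess is right 61.7% of the time.

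The documents do not support the stronger reading that enrolment is or will be steered. Bias is zero if nobody guesses, and any figure in mmHg depends on an assumed d. The trial is a pilot, its adherence and satisfaction results are descriptive, and blood pressure is secondary. Severity is minor; the change is worth making because it costs almost nothing.

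**What to change.** In the Phase II section, replace the stated block of 20 with a restricted scheme set in the existing online tool, and say that its parameters are withheld from everyone who enrols participants until enrolment closes.

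- **Preferred:** a maximum-imbalance (big-stick) rule with a limit such as 8. It suits a trial with no stated strata and brings correct guessing to about 52%.
- **Minimum:** block sizes varied at random among larger values, for example 16, 20, 24 and 28. This removes certain assignments but lowers guessing only to about 60%, so most of the exposure to guessing remains.
- **Avoid:** small random blocks of 4, 6 and 8, which raise guessing to about 68%.

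Reword the concealment sentence so that it says from whom the next assignment is hidden before enrolment, and treat blinding after assignment separately. If the full protocol already keeps enrolling staff apart from those who teach the app, one clause saying so would meet that part of the point.

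The cost is a tool setting and one or two sentences, with no added participants. The arms may end slightly unequal, as shown in the working, with a precision loss below 2%.

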## Methods

### Phase I: Design and Usability Testing of the mDASHNa-CC App

Adhering to a phased sequential approach to the development of complex technology-based interventions [54], the development of the mobile Dietary Approach to Stop Hypertension with Sodium (Na) Reduction for Chinese Canadians (mDASHNa-CC) app will include app design, usability testing, and feasibility testing. A user-centered design approach will be applied, where seniors will be actively engaged in all aspects of the research process, including the app’s design, the usability and feasibility testing, and the refinement of the prototype.

Convenience sampling will be used to recruit eligible individuals. To access the most representative sample of Chinese Canadian seniors, a community center in Toronto where Chinese Canadians occupy a high percentage of the total population will be used for blood pressure screening, participant recruitment, app testing, and participant follow-up. In partnership with the Ontario Chinese Senior Association, we will host blood pressure screening events in the Chinese community to facilitate the recruitment process. The app testing procedures will commence after participation eligibility is assessed, informed consent is obtained, and a trained research assistant collects demographic and other outcome data.

This study will include all Chinese Canadians who: (1) are at least 65 years old; (2) have a systolic blood pressure higher than 140 mmHg, or a diastolic blood pressure higher than 90 mmHg, or are on antihypertensive medications, based on preintervention baseline assessment; (3) can understand (listen) and speak in Mandarin or Cantonese, and can read and write in Chinese; and (4) have access to a smartphone. Since self-reporting has been recommended as the preferred approach to measure ethnicity and has been widely applied in public health studies [55,56], the identification of Chinese Canadians in this study will be based on self-reporting of ethnicity. The study will exclude individuals who: (1) have special dietary requirements; (2) are a household member of another mDASHNa-CC participant; or (3) plan to leave the area before the anticipated end of the study.

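### The Phase II exclusion list omits the household-member rule stated in Phase I, so people who share meals can be randomised to opposite arms, which would modestly dilute the between-arm contrasts

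*Protocol article*

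**What the plan says.** The Phase I section of the protocol article (Design and Usability Testing) lists three exclusions. One covers people who "are a household member of another mDASHNa-CC participant"; another covers those who "plan to leave the area before the anticipated end of the study".

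The Phase II section (Feasibility Testing) gives a separate numbered list. It opens "Individuals were excluded if they: (1) used antihypertensive medications, insulin, or oral hypoglycemic agents", continues with a recent cardiovascular event, heart failure and cancer, and closes "or (5) had special dietary requirements". Household membership and planned departure are absent. On what carries over from Phase I, the section states: "The sampling procedures and setting will be the same as the Phase I study". It says the same of the recruitment process and does not mention eligibility.

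Allocation in Phase II is 1:1, with 60 participants and a block of 20, and the unit is the individual participant. The Data Analysis and Statistical Methods section compares mean change scores for blood pressure, weight, waist circumference and quality of life with an independent two-sample t test. Nothing in the article provides for household randomisation, same-arm allocation or a clustered analysis.

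The language criteria also differ. Phase I takes people who "can understand (listen) and speak in Mandarin or Cantonese". Phase II takes those who "were able to understand and speak Mandarin and read and write Chinese".

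**The concern.** The intervention aims to change what people eat, and people in one household commonly share meals. Phase I consists of interview and think-aloud sessions with no control arm, so shared meals have no comparison to distort there. In Phase II a control participant who lives with an app user may eat part of the intervention diet and may see the app. That moves the control mean towards the intervention mean and shrinks the between-arm difference.

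The contrasts exposed are the secondary outcomes tested between arms. The DASH score and 24-hour urinary sodium, listed under adherence in the Phase II Measurement Tools section, are exposed in the same way if they are compared between arms. The article says the study should prepare a full randomised trial, so a diluted preliminary estimate would be carried into that trial's planning.

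**Working it through.** **Does the exclusion carry over?** The Phase II list is restated, and it conflicts with Phase I: antihypertensive medication is a route into Phase I and an exclusion in Phase II. It also repeats one Phase I exclusion, special dietary requirements. If the Phase I exclusions applied automatically, that repeat would be needless. Staff screening from the Phase II list would not apply a household rule.

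**Inputs from the article.** N = 60, 1:1, block of 20 (Phase II section). Earlier pilot: systolic difference 3.8 mmHg, t = −1.58 on 55 df, P = .12 (Preliminary Work section).

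**Inputs assumed.** f = share of participants who belong to an enrolled couple, 10–40%. c = share of the effect passed to the control spouse, 25–100%. ρ = within-couple correlation, 0.2–0.5. Two-sided alpha 0.05. Pilot arms of 28 and 29.

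**Reproducing the article's figures.** The 60 rests on feasibility recommendations with no effect size, SD or power, so there is no calculation to reproduce. The pilot's result is consistent: |t| = 1.58 on 55 df gives P = 0.120. The implied standard error is 3.8/1.58 = 2.41 mmHg, and the implied SD of change is 2.405/√(1/28 + 1/29) = 9.08 mmHg.

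**Chance that a couple is split.** In one block of 20 with 10 per arm, once the first member is placed, 10 of the 19 remaining places are in the other arm: 10/19 = 0.526. Over the full 60 with 30 per arm it is 30/59 = 0.508.

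**Exposed controls.** There are 60f/2 = 30f couples, of which 30f × 10/19 are split. Each split couple has one control, so the exposed share of the 30 controls is f × 10/19.

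**Diluted difference.** 3.8 × (1 − c × f × 10/19) mmHg. Illustrative power at 30 per arm and SD 9.08 is in brackets; with no couples the values are 3.80 (0.367).

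| f | c = 25% | c = 50% | c = 100% |
|---|---|---|---|
| 10% | 3.75 (0.359) | 3.70 (0.351) | 3.60 (0.336) |
| 20% | 3.70 (0.351) | 3.60 (0.336) | 3.40 (0.305) |
| 40% | 3.60 (0.336) | 3.40 (0.305) | 3.00 (0.248) |

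Between 99% and 79% of the difference is retained.

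**Rarer couples.** If only 2–6 of the 60 enrol as couples (also assumed), that is 1–3 couples and 0.53–1.58 split couples, or 1.8–5.3% of controls. With full spill-over the loss is 0.07–0.20 mmHg.

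**Treating spouses as independent.** The variance of the difference is multiplied on average by 1 + ρf(P same arm − P opposite arms) = 1 + ρf(9/19 − 10/19) = 1 − ρf/19. At f = 0.4 and ρ = 0.5 this is 0.99; at f = 0.1 and ρ = 0.2 it is 0.999. Same-arm and split pairs nearly cancel. At f = 0.4 and ρ = 0.5, a single sample could range from 0.80 (every couple split) to 1.20 (every couple in the same arm).

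**The case against.** **The rule may be meant for the whole study.** The Phase I section refers to the study as a whole, names feasibility testing as part of development, and words both rules in terms of the study rather than the phase. Phase II then keeps the sampling, setting and recruitment. This has some force: the article does not prove that the rule was dropped on purpose. It does not settle the matter, because Phase II rewrites its eligibility and repeats only one of the Phase I exclusions.

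**Couples may be few.** Both spouses would need to be at least 65, fall in the stated blood pressure range, take none of the excluded medicines, clear the other exclusions and have access to a smartphone. The article gives no count of couples and does not say that couples attend screening together. This objection stands, so the upper end of the range should not be read as the expected case.

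**Shared meals are not the whole intervention.** Education, daily self-assessment, feedback and rewards reach only the app user. This also stands, and it makes full spill-over an upper bound.

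**It is an unpowered pilot.** Blood pressure is secondary. Accrual, attrition, technical issues, acceptability and app-use counts are descriptive, and a diluted contrast does not bias them. The largest loss in the table, 0.80 mmHg, is a third of the pilot's standard error (0.80/2.41 = 0.33). That limits the weight of the point but leaves the omission in place.

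**Conclusion.** The point holds as a modest, correctable gap. As written, Phase II can randomise members of one household to opposite arms of a dietary trial, with no provision in allocation or analysis. The effect is a bias towards no difference. For systolic pressure it takes 3.8 mmHg to about 3.75–3.00 mmHg, and illustrative power from 0.37 to 0.36–0.25, under the assumed couple shares of 10–40% and spill-over of 25–100%. If couples are rarer, the loss falls to 0.2 mmHg or less.

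Three stronger readings are tempting, and the documents do not support them:

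- A reader might infer that counting spouses as independent also dilutes the effect. It changes the standard error and not the difference, and on average the variance factor is 0.99–1.00.
- A reader might take a loss of 10–20% as the likely size. That needs 20–40% of participants in couples together with full spill-over, and the article supports neither figure.
- A reader might treat the missing planned-departure rule and the Mandarin-only criterion as shown harm to attrition and accrual. The article gives no figure for either, a narrower population is a permissible choice, and the recruitment log would record reasons for ineligibility. These are inconsistencies between the two lists to be reconciled, and secondary to the household point.

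**What to change.** Add to the Phase II exclusions the Phase I wording, those who "are a household member of another mDASHNa-CC participant". If the rule was always meant to cover both phases, say so in the Phase II section.

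Alternatively, admit household members, allocate them to the same arm and account for household in the analysis.

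As a secondary edit, state whether the planned-departure exclusion applies in Phase II. Reconcile the language criteria as well, either by aligning them or by saying that the Phase II accrual result refers to Mandarin speakers.

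Cost: the exclusion needs only eligibility wording and one screening question. Each couple would contribute one person instead of two, so 3 more participants must be found if 10% would have enrolled in couples (6/2) and 12 at the 40% upper end (24/2). Accrual is therefore slightly slower, and the recruitment log would show why. Same-arm allocation avoids that but costs precision: the variance factor 1 + ρf is 1.02–1.20 over the assumed ranges, and the simple t test would need replacing.

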### Data Analysis and Statistical Methods

Demographic data will be analyzed using the software SPSS version 20.0 by a biostatistician. To describe the sample, various descriptive statistics (eg, means, standard deviations, proportions), dependent on the level of measurement of the variables, will be calculated for sample demographics and other baseline information. Descriptive statistics will be calculated to demonstrate how participants adhered to and are satisfied with the app. Open-ended questions will be reviewed by two researchers independently. Qualitative data will be organized into meaningful groups, combining similar patterns into themes. In feasibility testing, adherence is defined as 100% when 28/28 blood pressure entries and 14/14 dietary self-assessments entries are completed within the two weeks. An independent, two-sample, two-tailed *t* test will be used to examine the differences in mean change scores between the control and intervention groups regarding blood pressure, weight, waist circumference, and health-related quality of life.

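### The Phase II exclusion list omits the household-member rule stated for Phase I, so people who share meals could be randomised to opposite arms of a dietary trial

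*Protocol article*

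**What the plan says.** The article has two eligibility lists.

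- **Section 'Phase I: Design and Usability Testing of the mDASHNa-CC App'.** There are three exclusions. The second covers people who "are a household member of another mDASHNa-CC participant".
- **Section 'Phase II: Feasibility Testing of mDASHNa-CC App'.** The list starts "Individuals were excluded if they: (1) used antihypertensive medications, insulin, or oral hypoglycemic agents", continues with a recent cardiovascular event, heart failure and cancer, and closes "or (5) had special dietary requirements". Household membership is not on it.

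Two sentences in the Phase II section link back to Phase I: "The sampling procedures and setting will be the same as the Phase I study" and "The recruitment process of Phase II is the same as that of Phase I". Neither mentions eligibility.

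Phase II allocates 60 individual participants 1:1, in blocks of 20, to the app plus usual care or to usual care alone. Controls are offered the app only after the eight-week outcomes are collected. The 'Data Analysis and Statistical Methods' section uses an independent two-sample t test to "examine the differences in mean change scores between the control and intervention groups" and does not mention households.

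**The concern.** The rule appears in the phase that has no arms and is absent from the phase that has them. The intervention teaches a dietary pattern, sodium reduction and food therapy. These act through shopping and cooking, which members of a household often share. A control who lives with an app user may therefore receive part of the intervention during the eight weeks in which the design means controls to be unexposed.

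If the app works, such exposure biases the between-arm differences in blood pressure, weight and waist circumference toward zero. The same would apply to the DASH score and 24-hour urinary sodium if these are compared between arms. The planned t test cannot remove this bias afterwards. The 'Implications' section also presents the pilot as groundwork for a full trial, so the gap in eligibility could be carried forward.

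**Working it through.** **1. Is the rule carried into Phase II?** The two lists were compared item by item.

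| Item | Phase I | Phase II |
|---|---|---|
| Antihypertensive medication | a route to inclusion | excluded |
| Language | Mandarin or Cantonese | Mandarin |
| Special dietary requirements | excluded | excluded, restated |
| Household member of a participant | excluded | not listed |

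The Phase II list is separate and differs openly from the Phase I list. It repeats one Phase I exclusion and leaves this one out, so silent inheritance is not the natural reading.

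**2. Chance that a couple is split.** The inputs are 60 participants, 1:1 allocation and blocks of 20 (Phase II section).

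- Both in the same block: 10/19 = 0.526.
- Over the whole trial, 30 per arm: 30/59 = 0.508.

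**3. Dilution of the contrast.** The number of couples and the share of effect transferred are assumptions, since the article gives neither. Let p be the share of the 30 controls who live with an app user, and τ the share of the effect that reaches them. The expected contrast is then the true effect × (1 − p × τ). The larger split probability, 0.526, is used.

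| Couples assumed | Expected split | p = split/30 | Shrinkage, τ = 0.5 to 1 | Loss from 3.8 mmHg |
|---|---|---|---|---|
| 3 | 1.58 | 5.3% | 2.6% to 5.3% | 0.10 to 0.20 |
| 6 | 3.16 | 10.5% | 5.3% to 10.5% | 0.20 to 0.40 |
| 10 | 5.26 | 17.5% | 8.8% to 17.5% | 0.33 to 0.67 |

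The 3.8 mmHg is the systolic difference in the earlier classroom pilot ('Preliminary Work'), used here only as a scale. With 10 couples it would read as 3.8 × (1 − 0.088) = 3.47 down to 3.8 × (1 − 0.175) = 3.13 mmHg.

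**4. Comparison with precision.** The earlier pilot reports t = −1.58 on 55 degrees of freedom, which gives a standard error of 3.8/1.58 = 2.4 mmHg. The largest loss in the table is 0.67/2.4 = 0.28 of a standard error.

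**5. Independence in the t test.** With 30 per arm, k couples and within-couple correlation ρ, the variance of the difference relative to the independent case (2/30) is 1 − kρ/30 if every couple is split and 1 + kρ/30 if every couple is in the same arm. Averaged over randomisation it is 1 + (kρ/30)(1 − 2 × 30/59). For k = 3 to 12 and an assumed ρ of 0.1 to 0.3:

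- all couples split: 0.99 down to 0.88;
- all couples together: 1.01 up to 1.12;
- averaged over randomisation: 0.998 to 1.000.

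**The case against.** The strongest reply is that the household rule is study-wide. The Phase I section words its exclusions as those of the study and refers to participants in the app study generally, not to Phase I participants. The next item, about leaving the area before the study ends, suits a trial with follow-up better than a usability interview. The Phase II section then keeps the Phase I sampling and recruitment. A condensed article might simply not repeat the rule. This reading is possible, and it is why confidence is only moderate. It is weak, though: importing the Phase I list would also import criteria that Phase II contradicts, and Phase II took the trouble to restate dietary requirements. For the same reason, a reader might infer that the sponsor deliberately removed the rule. The text shows only that it is absent.

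The second reply is that the effect is small, and this largely stands. Ten couples would mean that 20 of 60 participants were pairs in which both members were at least 65, had blood pressure within the Phase II limits, were free of the excluded medication and conditions, and had access to a smartphone. That is an extreme. The primary outcomes are feasibility measures, and the article says that the pilot is not powered for hypothesis testing.

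Two stronger readings are tempting and are not supported:

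- A reader might infer that correlated pairs invalidate the t test. On average over randomisation the variance error is about nil. It becomes noticeable only if nearly all couples fall the same way, and split couples make the test conservative.
- A reader might infer that attrition, a primary outcome, would cluster because couples withdraw together. Nothing in the article bears on this, so no such claim is made.

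**Conclusion.** The point holds as a gap in the Phase II eligibility text. The household exclusion is not in the list that governs randomisation, and the carry-over sentences do not clearly restore it. Household members who share meals can therefore be placed in opposite arms, with bias toward zero in the secondary between-arm comparisons.

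The size cannot be determined from the article. Under the assumed 3 to 10 couples and half to full transfer, the shrinkage is about 3% to 18%, and the upper end needs both extremes at once. Even that loss is well within the sampling error of a trial of this size. Importance is minor to moderate, with moderate confidence. It is worth correcting because the exclusion is the sponsor's own, and because the exposure can be prevented before enrolment but not removed in the analysis.

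**What to change.** Add a sixth item to the Phase II exclusions: being a household member of another Phase II participant, with the first eligible member enrolling. Ask about it at screening, and enter it in the recruitment log, which already records reasons for ineligibility. If the Phase I rule was always meant to cover both phases, one sentence saying so is enough.

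If the sponsor prefers to keep couples, randomise the household as one unit and account for pairs in the analysis, for example with household-clustered standard errors.

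The first option costs one line and one screening question, and the target of 60 is unchanged. A few otherwise eligible spouses would be turned away. This slightly lowers accrual, which is itself a primary outcome, so these exclusions should be visible in the accrual report.
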